### Sample size determination

Since there is no previous clinical study on EA to improve the survival of patients with PCAS and given this trial's pilot nature, we will follow the recommendation of 20 participants or more to achieve sufficient precision based on the sample size calculation of a previous study [24]. We plan to recruit 50 participants since a 20% dropout rate is expected.

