### Randomization

Eligible patients enrolled in this trial will be randomly assigned to the EA or control groups in a 1:1 ratio. Randomization assignment will be carried out by a researcher ([name]) not involved in the treatment and assessment. This randomization will be run with a block randomization size of four by SPSS 17.0. The randomization block size will be concealed to guarantee rigorous methodology, and the allocation number will be sequentially assigned and stored. The unique code assigned to each newly eligible participant will be adequately preserved throughout this study. This procedure will ensure that each eligible patient could be assigned to either of the two groups with equal probability and that group assignment will not be influenced by the researchers. [name] and [name] will enrol and assign participants to interventions according to the preprepared allocation sequence. Considering that an included patient could withdraw from the study, their randomization number would be invalidated, so we will ultimately take the first 52–60 patients. Finally, the number of patients in these two groups may be different because of the actual procedures performed.

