### Outcome measures

The primary feasibility outcomes are as follows:Evaluate the acceptability and compliance of EA in PCAS as an additional intervention of usual care.Explore the feasibility of recruiting, randomizing, and retaining participants.Evaluate outcome measures’ appropriateness.Collect data for effect size calculation in future sample size calculating.Develop an appropriate protocol for further study.

The length of time for recruitment of 50 eligible patients, recruitment rate and dropout rate will be measured. Successful recruitment is defined as at least half (50%) of eligible patients enrolled, with a dropout rate of no more than 20%.

The secondary patient-centred outcomes include the following:We define a favourable neurological outcome as a cerebral performance category (CPC) score of 1 or 2 on the 28th day after the ROSC. We define an ROSC as a spontaneous pulse and blood pressure, an abrupt sustained increase in end-tidal CO_2_ partial pressure (PETCO_2_) (typically ≥ 40 mmHg), or spontaneous arterial pressure waves with intra-arterial monitoring.Neurological scores: Glasgow Coma Scale (GCS) score, CPC score, modified Rankin Scale (mRS) score, and cranial computed tomography (CT) findings;Evaluation of cardiac function: troponin and lactic acid levels and echocardiography parameters.Sequential Organ Failure Assessment (SOFA) scoresAcute Physiology and Chronic Health Evaluation (APACHE) II scoresLength of stay in the ICU, length of hospital stay, hospital mortality/discharge, and hospital costsAdverse events

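### The sample size is given both as 50 and as a range of 52–60, which allows for withdrawals twice and leaves the end of recruitment without a rule

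*Protocol article*

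**What the plan says.** Four parts of the protocol article bear on the number of patients.

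- **Sample size determination.** The starting point is a published recommendation: "we will follow the recommendation of 20 participants or more to achieve sufficient precision". The text does not say whether 20 is per group or in total. It continues: "We plan to recruit 50 participants since a 20% dropout rate is expected".
- **Randomization.** Patients are "randomly assigned to the EA or control groups in a 1:1 ratio". Then: "Considering that an included patient could withdraw from the study, their randomization number would be invalidated", "so we will ultimately take the first 52–60 patients". The section does not say what fixes the number within that range.
- **Outcome measures.** "The length of time for recruitment of 50 eligible patients, recruitment rate and dropout rate will be measured". Recruitment counts as successful if at least half of eligible patients are enrolled, "with a dropout rate of no more than 20" per cent.
- **Statistical analysis.** Participants who cannot continue or be followed up stay in an intention-to-treat analysis. The analysis is mainly descriptive, with no formal comparison of groups.

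**The concern.** The number to be randomised is a basic design item. Here it has two values that cannot both be the plan, because 50 lies outside 52–60. The reason given for the range is withdrawal, which is also the reason given for arriving at 50.

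This matters more than it would in many pilots. The primary outcomes are feasibility outcomes, and they include the time to recruit a stated number and a dropout rate judged against a fixed limit. If the number randomised is open, so is the denominator of that rate, and the recruitment-time outcome refers to a number that may not be the one enrolled.

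A second inconsistency lies behind the range. The Randomization section invalidates a withdrawn patient's number, while the Statistical analysis section keeps that patient in the analysis. It is then unclear whether such a patient counts as randomised, as a dropout, or as neither.

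**Working it through.** **Inputs.** Base figure 20 and dropout 20% (Sample size determination); two groups at 1:1 and the range 52–60 (Randomization); dropout limit 20% and recruitment figure 50 (Outcome measures).

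**1. Reproduce the stated 50.** Inflation for dropout: N = n / (1 − d).

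- 20 per group: n = 2 × 20 = 40, so N = 40 / 0.80 = 50. This matches exactly.
- 20 in total: N = 20 / 0.80 = 25. This does not match.

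The per-group reading reproduces the plan's figure, so 50 is arithmetically sound. What is missing is the statement that 20 is per group.

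**2. Compare 50 with 52–60.** The figure of 50 already expects 20% loss: 50 × 0.80 = 40 retained. At the same loss, 52 leaves 52 × 0.80 = 41.6 and 60 leaves 60 × 0.80 = 48. Both exceed the 40 on which the sample size rests. The upper end equals 50 × 1.2 = 60, as if a second 20% had been added. The article does not say how 60 was reached, so that match is only suggestive. The range spans 60 − 52 = 8 patients.

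**3. Effect on the dropout criterion.** Rate = dropouts / number randomised; success requires at most 20%.

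| Number randomised | 20% of that number | Most dropouts allowed | 11 dropouts |
|---|---|---|---|
| 50 | 10.0 | 10 | 22.0%, fails |
| 52 | 10.4 | 10 | 21.2%, fails |
| 56 | 11.2 | 11 | 19.6%, passes |
| 60 | 12.0 | 12 | 18.3%, passes |

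The result for 11 dropouts changes at 11 / 0.20 = 55, which lies inside the stated range. The table holds the dropout count fixed; patients added later could also drop out.

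**4. Withdrawals, side by side.** Under Randomization, the number is invalidated and the range is offered as the consequence. Under Statistical analysis, the patient remains in the intention-to-treat set. If the patient remains, no place has been vacated and a replacement serves no stated purpose. If the number is void, the analysis is not by intention to treat.

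**The case against.** The best defence is that the two figures describe different things: 50 patients retained, and 52–60 allocation numbers used to reach them. This would correspond to withdrawals of 1 − 50/52 = 3.8% to 1 − 50/60 = 16.7%. It does not fit the text, because the sample size section presents 50 as the number to recruit with 20% dropout already expected. It is also fair to say that this is a descriptive pilot, that the article disclaims power for clinical outcomes and says clinical results will be interpreted with caution, and that a few patients either way will not change its conclusions about clinical effect. That stands, and it limits the weight of the point.

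Stronger readings that a reader might infer are not supported:

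- *The stated basis gives only 25.* This requires 20 to be the trial total. In a two-arm trial, 20 per group is a natural reading and gives exactly 50.
- *There are three targets.* Only 50 and 52–60 are stated as targets.
- *Unblinded investigators can choose when to stop.* The article does not say who ends recruitment or that outcomes inform the decision, and it gives withdrawals as the reason for the range. Outcome evaluators, laboratory technicians and biostatisticians are to be blinded, and the person monitoring outcomes is outside enrolment and analysis. With no formal comparison planned, no type I error rate is at stake. An open end could still affect estimates, but nothing in the article shows that it would.
- *50 is wrong because it is not a multiple of the block size of four.* An incomplete last block shifts the balance by at most two patients, and the article already accepts unequal groups.
- *Precision is inadequate.* The article sets no precision criterion and gives no expected rate of favourable outcome, so there is no benchmark to fail.

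**Conclusion.** The point holds as an internal inconsistency, not as an arithmetic error. The article gives two recruitment targets that do not overlap, allows for withdrawals in both, and has no rule for ending recruitment within a range of 8 patients. The way withdrawals are handled under Randomization also conflicts with the intention-to-treat rule.

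The demonstrable consequence is for feasibility: a count of 11 dropouts fails the 20% limit at 50 or 52 and passes at 56 or 60. This assumes that the denominator is everyone randomised and that the dropout count is held fixed. The statement that 50 follows from the stated inputs assumes that the recommendation of 20 is per group, which the article does not say. The importance is moderate: the trial is descriptive, but recruitment and retention are what it is meant to measure.

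**What to change.** 1. In Sample size determination, state the derivation in full: 20 per group, 40/0.8 = 50 in total, once the investigators confirm that the recommendation is per group.
2. Set one fixed number randomised: 50, or 52 if complete blocks of four are wanted (13 × 4 = 52). Alternatively, write a stopping rule for recruitment that makes no reference to outcomes. The number already enrolled is not given; if it exceeds the chosen figure, the rule is the workable option.
3. In Randomization, delete the range of 52–60 and the invalidation of withdrawn patients' numbers. Keep every randomised patient, including those who withdraw, in the dropout denominator and in the intention-to-treat analysis, without replacement.
4. Use the same number in the recruitment-time outcome under Outcome measures.

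The cost is more than wording, because ending replacement changes a procedure. The Design section requires ethics approval for protocol changes, and the Trial status section says that recruitment is under way, so a small amendment is needed. With a fixed total, the trial could retain somewhat fewer patients than under the upper end of the range: at 20% dropout, 40 from 50 or about 41 to 42 from 52, against 48 from 60. The 40 is what the sample size section was built on.

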### Interventions and procedures

Eligible patients for whom consent is provided by the legal representative or the patient themselves will receive EA. In addition, participants will receive standard therapy according to American Heart Association guidelines for CPR recommendations [14, 25–27], while any other adjunct treatment will be prohibited. Investigators will be trained before the start of the study. [name], who will not be involved in participants’ enrolment or data analysis, will monitor the outcomes of the interventions at least once per month during the trial.

### Standard therapy

Standard therapy will be based on current recommendations [14, 25–27], including basic life support (BLS), advanced cardiovascular life support (ACLS), and postcardiac arrest care. BLS includes immediate recognition of SCA, EMS activation, early CPR, and rapid defibrillation. ACLS consists of airway control and ventilation, antiarrhythmic drugs and vasopressors during and immediately after SCA, and extracorporeal CPR. Postcardiac arrest care is considered coronary angiography, which will be performed in an emergency setting. Comatose adult patients with an ROSC after SCA will receive TTM; fever will be actively prevented in these comatose patients after TTM, and other standard critical care interventions will be administered.

### EA treatment

Disposable stainless steel acupuncture needles will be inserted at the Baihui acupoint (GV20, located at the intersection of the sagittal midline and the line linking the ears) and unilaterally on the side of the left leg at the Zusanli acupoint (ST36, situated on the front to one side of the leg, 3 *cun* below the acupoint ST35 and a cross-finger (middle finger) away from the leading edge of the tibia) to a depth of approximately 0.5 cm [28]. Furthermore, an EA instrument (Suzhou Medical Supplies Factory Co., Ltd., Jiangsu, China) will be connected to perform EA stimulation for 30 min using a dense-dispersed wave at frequencies of 20 and 100 Hz. The current intensity will be less than 10 mA (adjusted to induce a slight muscle twitch), and the pulse width will be 0.5 ms. One of the two electrodes of the EA stimulator will be connected to the needle at GV20, and the other electrode will be connected to the needle at ST36. This EA intervention will begin immediately after the ROSC for 20 min and will continue for up to 14 days, discharge, or death, whichever comes first. The EA will be performed by [name], [name], or [name], who will conduct the research and have previously received equal training.

### Principles of the formula

GV20 is located at the top of the apex, which is the intersection of three *yang* meridians of the hand, three *yang* meridians of the foot, and the governor vessel. At the same time, the head is the meeting of *yang* and the ancestor of meridian vessels. The functional brain injury after PCAS is located in the head, and the pathogenesis is *yin-yang* disharmony, the reversal of *qi* and blood reversal. Therefore, the choice of acupuncture at GV20, where vessels and *qi* converge, plays an essential role in regulating the body’s *yin-yang* balance [29, 30].

ST36 is the acupoint of the stomach meridian (ST), the *sea point* in the *five transport points*. The stomach is the sea of water and food and the source of *qi* and blood engendering transformation. It has an exterior and interior relationship with the spleen meridian (SP), and the spleen and stomach are the roots of acquisition. “Suwen” indicated that “the treatment of wilting disease takes *yang* brightness meridian alone.” Acupuncture at ST36 can stimulate the *qi* of the viscera and bowels, encourage the movement of qi and blood, and dredge the block of the meridian vessel [31].

EA at GV20 and ST36 can restore *yang* to prevent collapse and open the orifices. According to long-term experience, acupuncture used in our trials is considered safe for patients who suffer from SCA. However, according to modern clinical research principles, it has been criticized for a lack of adequate assessment. Therefore, we designed this observational trial to evaluate the efficacy of EA.

### Outcome measures

The primary feasibility outcomes are as follows:Evaluate the acceptability and compliance of EA in PCAS as an additional intervention of usual care.Explore the feasibility of recruiting, randomizing, and retaining participants.Evaluate outcome measures’ appropriateness.Collect data for effect size calculation in future sample size calculating.Develop an appropriate protocol for further study.

The length of time for recruitment of 50 eligible patients, recruitment rate and dropout rate will be measured. Successful recruitment is defined as at least half (50%) of eligible patients enrolled, with a dropout rate of no more than 20%.

The secondary patient-centred outcomes include the following:We define a favourable neurological outcome as a cerebral performance category (CPC) score of 1 or 2 on the 28th day after the ROSC. We define an ROSC as a spontaneous pulse and blood pressure, an abrupt sustained increase in end-tidal CO_2_ partial pressure (PETCO_2_) (typically ≥ 40 mmHg), or spontaneous arterial pressure waves with intra-arterial monitoring.Neurological scores: Glasgow Coma Scale (GCS) score, CPC score, modified Rankin Scale (mRS) score, and cranial computed tomography (CT) findings;Evaluation of cardiac function: troponin and lactic acid levels and echocardiography parameters.Sequential Organ Failure Assessment (SOFA) scoresAcute Physiology and Chronic Health Evaluation (APACHE) II scoresLength of stay in the ICU, length of hospital stay, hospital mortality/discharge, and hospital costsAdverse events

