**Trial registration:**

chictr.org.cn: ChiCTR2000040040. Registered on 19 November 2020. Retrospectively registered. http://www.chictr.org.cn/.

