Nevertheless, the effects of acupuncture on PCAS have never been investigated comprehensively. Therefore, the present pilot, randomized, controlled study was designed to explore the feasibility of electroacupuncture (EA) on PCAS patients and furthermore evaluate the impact in the main trial.

The specific objectives of this pilot study were to test the trial procedures, explore the feasibility of the program, and provide data for recruitment, follow-up rates, and sample size calculation for the main trial.

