### Trial status

We are currently recruiting participants.

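### The definition of successful recruitment has no time element, so slow accrual cannot fail it, although time to recruit is measured and feasibility of recruiting is a primary outcome

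*Protocol article*

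**What the plan says.** The Background section gives as one objective of the pilot to "provide data for recruitment, follow-up rates, and sample size calculation for the main trial". Among the primary feasibility outcomes under Outcome measures is "Explore the feasibility of recruiting, randomizing, and retaining participants".

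The same section then names what will be recorded: "The length of time for recruitment of 50 eligible patients, recruitment rate and dropout rate will be measured". The sentence that follows sets the pass mark: "Successful recruitment is defined as at least half (50%) of eligible patients enrolled, with a dropout rate of no more than 20" per cent.

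The target comes from Sample size determination: "We plan to recruit 50 participants since a 20% dropout rate is expected". The Randomization section speaks instead of finally taking 52 to 60 patients. The article gives no planned recruitment period, no target accrual per month and no limit on the time taken.

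Three dated facts bear on accrual. The registration entry reads "Registered on 19 November 2020. Retrospectively registered", the article is dated 13 January 2023, and Trial status says "We are currently recruiting participants".

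**The concern.** The protocol names three recruitment quantities and then builds its definition of success without the first of them, time. The term *recruitment rate* does not close the gap. If it means patients per month, it is measured but has no threshold. If it means the share of eligible patients enrolled, it is the 50% test and time is still absent.

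The share enrolled and the dropout rate describe uptake and retention among patients who present. They do not describe how many present. Entry is narrow: in-hospital arrest from respiratory failure or hypovolaemic shock, cardiogenic causes excluded, Glasgow coma score of 8 or less, in two units. A small flow of eligible patients is therefore a plausible limit on recruitment, and the definition cannot detect it. At stake is whether the label *successful recruitment* can be read as evidence on feasibility when the months needed to reach 50 patients have no bearing on it.

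**Working it through.** **1. The plan's own figure.** Sample size determination says "we will follow the recommendation of 20 participants or more to achieve sufficient precision". Read as 20 per arm, 2 × 20 = 40, and 40 / (1 − 0.20) = 50, which matches. Read as 20 in total, 20 / 0.80 = 25, which does not. The target of 50 is thus reproduced on the per-arm reading, and it involves no time.

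**2. The rule against time.** Success requires enrolled / eligible ≥ 0.50 and dropouts / enrolled ≤ 0.20. Take 100 eligible, 50 enrolled and 10 dropouts: 50/100 = 50% and 10/50 = 20%, so both tests pass.

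| Months to enrol 50 | Patients per month | Verdict |
|---|---|---|
| 6 | 50/6 = 8.33 | success |
| 24 | 50/24 = 2.08 | success |
| 60 | 50/60 = 0.83 | success |
| 120 | 50/120 = 0.42 | success |

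The number of months appears in neither ratio, so any positive accrual rate can pass.

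**3. What the dates suggest.** 19 November 2020 to 13 January 2023 is 25.8 months. Assume that recruitment had begun by registration (which was retrospective), that the status sentence was true at publication, and that no more than 50 patients were in. Accrual was then at most 50 / 25.8 = 1.94 per month over two units, or 0.97 per unit. With 60 patients the ceiling is 60 / 25.8 = 2.33. If the status sentence was written a year before publication, the ceiling is 50 / 13.8 = 3.6 per month, or 1.8 per unit. The range is about 2 to 4 per month. It is a ceiling under these assumptions, not an estimate.

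**4. Whether this rules out a main trial.** The documents give no main-trial size, so this is an illustration. Assume two-sided 5%, 80% power, 1:1 allocation and 20% dropout. The Background's mortality of 65–80% implies survival of 20–35%. Take 20% as the control rate, although this is survival and not favourable neurological outcome. A comparison of 20% with 35% then needs 345 patients, and 20% with 30% needs 735.

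| Ceiling for two units | Units in main trial | 345 patients | 735 patients |
|---|---|---|---|
| 1.94 per month | 2 | 14.8 years | 31.6 years |
| 1.94 per month | 10 (9.7 per month) | 36 months | 76 months |
| 3.6 per month | 10 (about 18 per month) | 19 months | 41 months |

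The rates are ceilings, so these are minimum times. The answer runs from under two years to over thirty, depending mainly on an assumed number of units. The documents do not settle it.

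**The case against.** The strongest reply is that nothing is lost. The rule defines successful recruitment, not success of the pilot, and no section makes it a condition for going on to the main trial. The objective is to supply recruitment data; time to 50 patients will be measured, and the Statistical analysis section promises a descriptive analysis aimed at estimation. A reader can judge the months taken. The first part stands: this is not a go/no-go rule for the whole pilot. The second does not remove the defect. Once a pass mark is fixed for recruitment, a measured time without a threshold leaves the judgement on speed to be made afterwards, beside a label that may already say success.

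A reader might also infer that the pilot could pass while the main trial could never be filled, or would take decades. The documents do not support that. The long durations above require the main trial to stay in the same two units. The Discussion says that the population was narrowed at the ethics committee's suggestion and that the research will be expanded next. Nor do the dates show that scarce eligible patients are the cause of any slow accrual; low consent would slow it too, and the 50% test could detect that.

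Two further cautions stand. Recruitment is under way, so a threshold chosen now by people who know the accrual would not be prespecified in any useful sense. And the unseen full protocol may state a recruitment period. That would not alter the definition printed in the article, which is given without reference to one.

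**Conclusion.** The point holds as a defect in the stated definition. Recruitment can be called successful however slow accrual is, because both tests are ratios of counts. This follows from the text alone and rests on no assumption. It matters because feasibility of recruiting is a primary outcome and recruitment data for the main trial are an objective.

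The practical size is not known. Accrual may be at or below about 2 to 4 patients per month over two units, subject to the assumptions on start date, status date and numbers enrolled. Whether that suffices depends on main-trial size, units and duration, which are not given. This is a cheap improvement to a feasibility criterion; it is not evidence that the main trial is infeasible.

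**What to change.** **Preferred.** Add an accrual element to the definition under Outcome measures: recruitment is successful only if, in addition, at least *r* patients are randomised per unit per month, where *r* = main-trial size / (units × months). The sponsor supplies its own provisional values. The threshold should be set by someone without sight of accrual to date, and dated as an amendment.

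**If that cannot be done credibly now.** State that the 50%/20% rule concerns uptake and retention only. Base the conclusion on recruitment feasibility on the accrual rate per unit per month with a 95% confidence interval, and on the main-trial duration it implies for stated numbers of units.

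Under either option, say whether *recruitment rate* means patients per month or share of eligible patients, and which count ends the clock, since 50 and 52–60 both appear.

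**Cost.** Wording and existing randomisation dates; no change to treatment, visits or data collection. The pilot may fail a criterion that it would otherwise pass. The sponsor must state provisional main-trial assumptions before the pilot has informed them. The Design section requires any protocol change to go to the Institutional Review Board for approval.
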